### **BACKGROUND**

#### **Atrial Flutter**

Atrial flutter (AFL) is a common cardiac rhythm abnormality, with considerable morbidity. Whilst data in the UK population is not available, US studies suggest an overall incidence of 88/100,000 person-years, rising to 587/100,000 in subjects older than 80, and being 2.5 times more common in men (FIGURE 1). Extrapolation of these data to an adult UK population would suggest 35,000 new diagnoses of AFL per year. This increase in incidence with age mirrors the burden of atrial fibrillation, a closely related arrhythmic condition. AFL commonly coexists with other disease states such as hypertension, heart failure and chronic respiratory disease, adding a potentially modifiable additional burden to these conditions. It can be significantly symptomatic for the patient, negatively impacting quality of life, and the cause of considerable morbidity with persistent rapid palpitations, breathlessness, lack of energy and a need for long term rate controlling drug therapy often at the expense of side effects. Electrical cardioversion is often only a temporary respite; in one study 92% of patients had a recurrence of flutter with medical therapy or cardioversion.

#### **Catheter ablation of atrial flutter**

Catheter ablation for AFL is a well-established and routinely practiced treatment. Ablation is more effective than the limited options for drug therapy. Acute procedural success defined by bidirectional isthmus block is more than 95%, however there is a long term recurrence rate of 5-10% at a mean follow up of eight months. Bidirectional conduction block is the required endpoint for AFL ablation. The principle reason behind this is recovery of isthmus conduction. Poor tissue contact and inadequate energy delivery are the main cause of this. In order to improve success rates, three dimensional mapping systems are used to allow operators to mark lesion placement, and help in the creation of a straight and complete line of ablation. Until recently, catheter contact during ablation was determined using surrogates such as lack of catheter motion, electrogram attenuation and electrical impedance drops. Added information with regard to tissue contact is particularly pertinent to this procedure as anatomical variations typical to this region of the heart, with thick ridges of heart muscle and undulations of tissue, reduce the success of ablation.

#### **Contact technology**

There has been much interest in the development of technology to determine tissue catheter contact, and lesion depth. Contact information has been shown to gauge lesion size, with increased contact also being related to steam pops and thrombus formation. There are currently three technologies in use. The first uses an optical fibre at the tip of the catheter to sense the contact force time integral (Tacticath, Endosense SA, Geneva, Switzerland). The second is the Thermocool Smart Touch Catheter (Biosense Webster, Diamond Bar CA, US) which has a spring at the tip of the ablation catheter which deforms as pressure is applied; this measures contact force directly. This is used in conjunction with the CARTO-3 3D mapping system (Biosense Webster, Diamond Bar CA, US). The third technology is the Ensite Verisense System (St Jude Medical, St Paul MN, US) calculates the electrical coupling index (ECI) derived from tissue resistance and reactance. This is used in conjunction with the Ensite NAVx Velocity 3D mapping system (St Jude Medical, St Paul MN, US). It is clear that the ability to quantify the catheter tissue interface is important, however there has not been a head to head comparison between contact force and ECI. Therefore it is not possible to know whether contact force or ECI have any advantages over each other or are any better than conventional techniques when considering catheter ablation of atrial flutter.

It is important to determine whether the relative advantages of each technology translate to clinical benefit. We therefore aim to investigate the differences in radiofrequency (RF) energy application time, procedure duration and outcomes between conventional ablation, contact force and ECI.

## **HYPOTHESES**

We hypothesise that:

1. The use of either contact force or ECI will result in lower procedure time, reduced RF requirements and improved outcomes compared to the conventional approach.
2. There would be no difference in outcome measures between contact and ECI, as both provide the operator with information about the tissue catheter interface.

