### Sample Size

Previous studies have focussed on number of RF lesions (mean typically 12 – 19) and total procedural time (mean typically 100-150mins), along with fluoroscopy time (mean typically 2-10 mins). No local data is available to guide timings for bidirectional block using different catheter technologies and mapping systems. Therefore based on prior publications, a sample size of 120 patients is sufficient for this feasibility study i.e. 30 patients in each group.

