### Statistical methods

Continuous variables will be checked for normality. If they are normally distributed the results will be expressed as mean  $\pm$  SD and compared by Student's t-test or ANOVA. If they are skewed the results will be expressed as median and interquartile range, and compared using the Mann Whitney U test. A chi-squared test will be used to compare categorical variables. A p value <0.05 will be considered statistically significant. Alternative statistical methods and additional analyses will be conducted as deemed appropriate.

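### Hypothesis 2 (no difference between contact force and ECI) is paired only with difference tests at p<0.05, which cannot support it, least of all with 30 patients per group

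*Protocol*

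**What the plan says.** The Hypotheses section of the protocol makes two statements. The first expects either sensing technology to beat the conventional approach. The second is about the two technologies themselves: "There would be no difference in outcome measures between contact and ECI". Study Design then says that the trial is performed to examine these hypotheses, so the second is a question that the trial sets out to answer.

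Statistical methods gives the tools. Normally distributed outcomes are "compared by Student's t-test or ANOVA", skewed ones are "compared using the Mann Whitney U test", and for the rest "A chi-squared test will be used to compare categorical variables". The single criterion is "A p value <0.05 will be considered statistically significant". The section closes with an open clause: "Alternative statistical methods and additional analyses will be conducted as deemed appropriate".

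Sample Size states that "a sample size of 120 patients is sufficient for this feasibility study i.e. 30 patients in each group". The figure rests on a cited pilot-study recommendation. No effect size, SD or power is given, and the section notes that no local data exist on times to bidirectional block.

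**The concern.** A difference test takes equality as its null hypothesis. A small p-value counts against equality, but a large one does not count for it, because it also arises when the sample is too small to show a difference that exists. Hypothesis 2 puts the expected finding in the null, and every named test treats that null as the default.

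This gives a perverse incentive: the fewer the patients and the noisier the outcome, the more likely the data are to look consistent with hypothesis 2. The Background notes that no head-to-head comparison of contact force and ECI has been made, and the section on expected value presents the trial as giving insight into whether either has specific advantages. A non-significant result taken as confirmation would answer that question from absence of evidence.

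**Working it through.** **Inputs**
- Patients per group: 30 (Sample Size). 120/30 = 4 groups. The randomisation figure is not shown, so four groups is an inference, but it makes unblinded contact force v unblinded ECI a 30 v 30 comparison.
- Significance level: 0.05 (Statistical methods). Sidedness is not stated; two-sided is assumed.
- Primary outcome: time to bidirectional block in seconds (Outcome measures), treated as continuous.
- SD and effect size: not given. Differences are in SD units over an assumed range.
- Recurrence: 5–10% at a mean of eight months (Background), used only as an illustration because this trial follows patients for six months.

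**The plan's own figure.** There is no power calculation to reproduce. The arithmetic is consistent: 4 × 30 = 120, and the Funding section gives £48,000/(£300 + £100) = 120.

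**1. How often is a true difference non-significant?** For a two-sample t-test with n = 30 per group, df = 58, the critical value is 2.002 and the noncentrality is d × √(30/2), where d is the true difference in SD units. For d = 0.5 it is 0.5 × 3.873 = 1.936. The noncentral t distribution then gives:

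| True difference (assumed) | Power | Non-significant |
|---|---|---|
| 0.2 SD | 12% | 88% |
| 0.3 SD | 21% | 79% |
| 0.5 SD | 48% | 52% |
| 0.7 SD | 76% | 24% |
| 0.8 SD | 86% | 14% |
| 1.0 SD | 97% | 3% |

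The Mann–Whitney test, approximated with relative efficiency 0.955, changes little (about 47% power at 0.5 SD).

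**2. What would an interval show?** The half-width of the 95% confidence interval is 2.002 × √(2/30) = 2.002 × 0.258 = 0.52 SD. An observed difference of exactly zero would still leave differences of about half an SD, in either direction, compatible with the data.

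**3. Recurrence, 5% v 10%, 30 v 30.** All pairs of event counts were enumerated, weighted by their binomial probabilities, and those with p<0.05 summed:
- uncorrected chi-squared: power 10.6%;
- continuity-corrected chi-squared or Fisher's exact test: power 1.9%.

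The protocol names chi-squared without saying whether it is corrected, so both are shown. About nine trials in ten or more would be non-significant. Roughly 435 patients per group would be needed for 80% power.

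**4. Could the trial show equivalence?** Suppose the true difference is zero and equivalence is claimed when the 90% interval lies inside the margin (two one-sided tests at 0.05). Simulated t-based power at 30 per group is about 22% for a margin of 0.5 SD and 78% for 0.75 SD. By the normal formula n = 2 × ((1.645 + 1.282)/margin)², 80% power needs 69 per group at 0.5 SD and 31 at 0.75 SD. These margins are assumptions; the protocol supplies nothing from which to justify one.

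**5. Sensitivity to the number of groups.** If there were instead three groups of 40, power at 0.5 SD would be about 61% (normal approximation), which leaves the conclusion unchanged.

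**The case against.** A reader might infer that the protocol adopts p>0.05 as the rule for confirming hypothesis 2. It does not. Statistical methods says only what counts as significant, and no section says that a non-significant result will be reported as no difference. Nor does the protocol state conclusions; it states hypotheses, and the second can be read as an expectation with its rationale attached. The problem is therefore a mismatch that invites a wrong reading, not a wrong decision rule in writing.

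It is also too strong to say that hypothesis 2 can be judged only by difference tests. The closing clause on alternative methods would permit intervals or an equivalence analysis. But it commits to neither, and a margin chosen under it after seeing the data would carry no weight.

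The protocol calls itself a feasibility study. That is a fair answer to the absence of a power calculation, and low power for this comparison is to be expected. It does not answer the pairing of a no-difference hypothesis with significance tests: a small sample is a reason to estimate.

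Finally, a statistical analysis plan may exist, and margins or interval reporting are commonly left to it. Their absence here is not the point. The point is that two things the protocol does state do not fit together.

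Large differences would usually be detected, as the table shows at 0.8 SD and above. The difficulty is with small and moderate ones.

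**Conclusion.** The concern holds in this form: the protocol states a no-difference hypothesis, says the trial will examine it, and names only methods that cannot support it. At 30 v 30, non-significance is more likely than not for true differences up to about 0.5 SD, and very likely for a recurrence difference of 5% v 10%. The figures rest on a two-sided 5% level, four groups of 30 and assumed effect sizes in SD units; how often a difference would be missed depends directly on those effects. Severity is moderate. The remedy is a matter of wording and reporting, and nothing about allocation, treatment or data collection is affected.

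**What to change.** - Reword hypothesis 2 as an estimation aim: to estimate the difference between contact force and ECI in each outcome.
- In Statistical methods, commit to reporting the contact force minus ECI difference (or the ratio of times, for skewed durations) with a 95% confidence interval for each outcome.
- State that p>0.05 will not be read as evidence of no difference.
- Make no equivalence claim unless a clinically justified margin is fixed before results are seen. With no SD in the protocol, such a margin is hard to defend now; without one, report the interval and leave the question open.

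The cost is a few sentences in two sections and no extra patients. The downside is that the trial will probably be unable to claim that the two technologies are equivalent, but 30 per group could not have sustained that claim except against a wide margin.

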## **STUDY DESIGN**

In order to examine these hypotheses we aim to perform a multicentre prospective, randomised study comparing RF energy time, procedure duration and outcome of catheter ablation of AFL between non-contact 3D guided ablation (i.e. blinded to contact or ECI sensing), contact force sensing and the assessment of ECI. Patients will be followed up for 6 months post procedure.

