## **STUDY PROTOCOL**

### Pre –procedure

Study participants will be randomized using block envelopes to undergo the procedure either blinded (control) or un-blinded to contact force or ECI. CARTO-3 or NAVx Velocity will be used as the 3D mapping systems for contact force and ECI catheters respectively. The procedures will be performed with patients in the post-absorptive state under conscious sedation or general anaesthesia.

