### Patient preparation and procedure.

As per standard practice, oral anticoagulation will be administered to the majority of patients who will then go on to have the procedure performed with uninterrupted warfarin (INR 2-3.5). Depending on randomisation, either the Ensite or CARTO-3 mapping system will be used, and the respective reference patches will be applied to the patient in the cardiac catheter laboratory. Venous sheaths will be inserted into the right and/or left femoral veins. A decapolar catheter will be inserted into the coronary sinus, and a quadripolar catheter into the right ventricle. An additional 20 pole Halo diagnostic catheter (Biosense Webster, Diamond Bar CA, US) can be placed around the tricuspid valve annulus as per operator preference. The creation of three dimensional right atrial geometry will be left to the discretion of the operator and is not a requirement.

A flutter line will be created by either a drag approach or point by point ablation using an irrigated tip Thermocool Smart Touch (Biosense Webster, Diamond Bar CA, US), or an Ensite Verisense catheter (St Jude Medical, St Paul MN, US). In the control group the operator will be blinded to contact force or ECI, by closing the respective sensing information windows on the 3D mapping system. Energy will be delivered at each point for a minimum of 30 seconds with flow limited to 17ml/min and power limited to 40W with a maximum temperature of 48°C. If bidirectional block is not achieved on the first pass, additional ablation targeting gaps will be applied. Following bidirectional block, a waiting time of 30minutes will be observed to check for, and react to, isthmus re-conduction. The procedure will end at this stage.

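### The sample size implies four groups but the stated comparisons name three; state the four arms and compare unblinded with blinded operators within platform

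*Protocol*

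**What the plan says.** **Three groups.** The aim, at the end of the Contact technology section, is to study "outcomes between conventional ablation, contact force and ECI". STUDY DESIGN repeats the three-way comparison and makes the control a single group: "non-contact 3D guided ablation (i.e. blinded to contact or ECI sensing), contact force sensing and the assessment of ECI". Hypothesis 1 also has one comparator: "The use of either contact force or ECI will result in lower procedure time, reduced RF requirements and improved outcomes compared to the conventional approach". Hypothesis 2 expects no difference between contact force and ECI, and gives as the reason that both inform the operator about the catheter-tissue interface.

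**Four groups.** Sample Size states that "a sample size of 120 patients is sufficient for this feasibility study i.e. 30 patients in each group". The Pre-procedure section ties each technology to its own system: "CARTO-3 or NAVx Velocity will be used as the 3D mapping systems for contact force and ECI catheters respectively". The section on patient preparation adds: "Depending on randomisation, either the Ensite or CARTO-3 mapping system will be used". It also says that control operators are kept from seeing whichever reading their system provides, so controls exist on both platforms.

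**Analysis.** Statistical methods lists general tests. Normally distributed outcomes are to be "compared by Student's t-test or ANOVA", skewed ones by Mann-Whitney, with significance at p<0.05. It does not say how many groups are compared or whether the two kinds of control are pooled.

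**The concern.** The platform is fixed by the technology: contact force is always CARTO-3 and ECI is always NAVx/Ensite. A control group drawn from both platforms therefore does not match either technology arm. Set against it, contact force differs in sensing and also, for half of the controls, in catheter and mapping system. The same holds for ECI. In the head-to-head comparison, catheter, mapping system and sensing all change together.

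A difference between catheters or mapping systems could then be read as an effect of contact information, or could hide one. The protocol gives no ground for taking the platform difference as nil: Sample Size says that no local data exist on time to block across these catheters and mapping systems.

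**Working it through.** **1. Number of groups.** From Sample Size, 120 / 30 = 4. Three groups of 30 would be 90, and 120 over three equal groups would be 40 each. A 60:30:30 split would total 120 but would not give 30 in each group. FUNDING confirms the total: 120 × (£300 + £100) = £48,000, the sum sought, whereas 90 patients would give £36,000. The layout that fits all the text is:

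| | Sensing hidden (control) | Sensing visible |
|---|---|---|
| CARTO-3 | 30 | 30 (contact force) |
| NAVx/Ensite | 30 | 30 (ECI) |

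**2. Bias by contrast.** Let P be the platform difference in SD units, with no effect of sensing. P is an assumption, because the protocol gives no value.

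- One technology (30) v pooled control (30 + 30): the control mean lies midway between the platforms, so the bias is P/2.
- Contact force (30) v ECI (30): bias P.
- Both unblinded arms (60) v both control arms (60): the platforms balance, so the bias is 0.
- Unblinded v blinded on one platform (30 v 30): bias 0.

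**3. Chance of a significant result with no sensing effect.** Normal approximation, within-group SD of 1, two-sided 5% assumed (the protocol does not state sidedness).

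- One technology v pooled control: SE = √(1/30 + 1/60) = 0.224. Pooling two platforms inflates the estimated SD to √[(88 + 60·P²/4)/88]. At P = 0.5 this is 1.021, so the critical difference is 1.96 × 1.021 × 0.224 = 0.448 against a bias of 0.25. The rejection rate is 19%.
- Contact force v ECI: SE = √(2/30) = 0.258, so the critical difference is 1.96 × 0.258 = 0.506. At P = 0.5 the rejection rate is 49%.

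| Assumed P (SD) | One technology v pooled control: bias | Significant | Contact force v ECI: bias | Significant |
|---|---|---|---|---|
| 0 | 0 | 5% | 0 | 5% |
| 0.25 | 0.125 | 8.5% | 0.25 | 16% |
| 0.5 | 0.25 | 19% | 0.5 | 49% |
| 0.75 | 0.375 | 35% | 0.75 | 83% |
| 1.0 | 0.5 | 55% | 1.0 | 97% |

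A simulation with t-tests (20,000 runs) gave 18.4% and 48.0% at P = 0.5, in agreement.

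**4. What the four-group layout can detect.** Detectable difference at 80% power = (1.960 + 0.842) × SE.

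- Within one platform, 30 v 30: 2.802 × √(2/30) = 0.72 SD.
- Sensing stratified by platform, 60 v 60: 2.802 × √(2/60) = 0.51 SD.
- Contact force gain minus ECI gain (interaction): 2.802 × √(4/30) = 1.02 SD. Its 95% CI half-width is t(0.975; 116) × √(4/30) = 1.98 × 0.365 = 0.72 SD.

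**The case against.** A reader might infer that the trial will be analysed as three groups and that its sensing effect is confounded with platform throughout. The protocol does not support that.

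- Statistical methods fixes neither the number of groups nor any pooling. ANOVA need not be one-way, and the section allows other methods. A statistical analysis plan, not at hand, may settle the model.
- The four arms are themselves inferred. The text gives no arm count, and Figure 2 may already define them, in which case STUDY DESIGN is a loose summary.
- Hypothesis 1 can be read as sensing of either kind against control, which is the unbiased 60 v 60 contrast.
- Each sensing technology comes with its own mapping system, so a head-to-head of whole systems is a legitimate question.
- The error rates rest on an assumed platform shift, and the study is called a feasibility study.

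Most of this stands, and it limits the point to the stated comparisons; the implied randomisation is sound. It does not remove the point. If Figure 2 shows four arms, the aim, hypotheses and design section still need to match it; if it shows three, 30 per group is wrong. Hypothesis 1 can equally be read as each technology against the mixed control. Hypothesis 2 goes beyond comparing systems, because it explains the result by contact information. The feasibility label does not remove the bias, and tests at p<0.05 are planned.

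**Conclusion.** The point holds in limited form. The count of groups is inconsistent: three are named in the aim, hypotheses and design section, four are implied by the sample size and procedure text. Taken as written, a single technology against the mixed control carries half of any platform difference. Contact force against ECI carries all of it and cannot be credited to sensing in the way hypothesis 2 does.

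The rates of false significance illustrate this for assumed shifts and do not predict what will happen; with no platform difference they fall to the nominal 5%. They also assume 30 per arm, normal outcomes, and, for the first contrast, pooled controls, which the protocol does not specify. The layout that the numbers imply can separate sensing from platform, so the remedy lies in how the arms and contrasts are stated.

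**What to change.** - Bring the aim, HYPOTHESES and STUDY DESIGN into line with Sample Size by stating four arms of 30: CARTO-3 blinded and unblinded, NAVx blinded and unblinded. Confirm that Figure 2 agrees.
- Test the effect of sensing as unblinded v blinded, stratified by platform (60 v 60). A two-factor model or a rank test stratified by platform would serve.
- Compare each technology only with the blinded control on its own platform.
- Report contact force v ECI as a comparison of whole systems. For the sensing question, report the difference in within-platform gains, (contact force − CARTO-3 control) − (ECI − NAVx control), with its CI, and reword the reasoning in hypothesis 2 to match.

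The cost is wording and a platform term, with no extra patients or data. The downside is that the difference in gains is imprecise (95% CI half-width about 0.72 SD) and must be reported as such.
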